#### Exposure Measures

The exposure measures of interest include demographic variables, clinical data, and treatment-related factors. Demographic variables include age, gender, height, weight, and ethnicity. Clinical data are composed of health care factors (comorbidity, smoking status, family history of tumors); tumor factors (pathology, gene detection, tumor segments, and metastatic status); radiological variables (computerized tomography, magnetic resonance imaging, x-ray, positron emission tomography–computerized tomography, and degree of epidural spinal cord compression); and clinical variables, which include onset time, general status (KPS, ECOG score), neurological function (ASIA score), pain (VAS value), and ambulatory status. Treatment-related factors include operation approach, operation time, blood loss, postoperative hospital stay, adjuvant therapies, etc.

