**Methods:**

This is a prospective cohort study, with an anticipated sample size of 240 patients (120 patients in the surgical group and 120 patients in the nonsurgical group). We will collect baseline data, including demographic, clinical, and radiological information, as well as data from patient-reported questionnaires. Patients will be followed up at 3, 6, 12, and 24 months after treatment, and survival status will be assessed every 3 months. The primary outcome is the overall survival period. Prognostic factors associated with overall survival will be analyzed by univariate and multivariate Cox proportional hazards regression. Odds ratios with 95% CIs will be presented. Statistical significance is set at *P*<.05.

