### Objective

In our study, a prospective, specific disease cohort of SMLC will be used to compare the effectiveness of surgical treatment and nonsurgical treatment. This study will provide useful information to explore the role of surgical treatment in comprehensive SMLC treatment and develop suitable treatment guidelines.

The primary aim of this study is to investigate and compare treatment outcomes in patients with SMLC. In addition, we also plan to analyze various prognostic factors of SMLC, such as treatment modalities, tumor subtypes, pre- and postoperative neurological function, and more.

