### Sample Size and Study Timeline

In this study, we plan to compare the overall survival (OS) time between the two groups and explore its prognostic factors. The sample size calculation was based on the survival time and estimation of influencing factors. According to an unpublished retrospective study performed at our center and previous literature [20,21], the average OS time was 11 (SD 4) months in the surgical group and 9 (SD 3) months in the nonsurgical group. Assuming an overall Type 1 error (α) of .05 and Type II error (β) of .1, we need 66 patients in each group. Additionally, there are 12 predictive factors we plan to analyze in the prediction model. According to the sample size estimation method for multivariable regression models, 100 cases in each group are needed (the ratio of surgical to nonsurgical group is 1:1). Considering a final follow-up rate of 80%, a minimum of 120 patients will be required for each group. There were approximately 25 patients undergoing surgery per year at our center; therefore, we plan to enroll the patients over the next 5 years. Since more patients are treated nonsurgically than surgically, all nonsurgical patients treated during the first 5 years will be enrolled.

The study duration is estimated to be 7 years to ensure that all recruited patients are followed up for 2 years. Each visit’s timeline and tasks are presented in Multimedia Appendix 1.

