### Statistical Analysis

Statistical analysis will be performed using SPSS for Windows (version 20; IBM Corp). The Lilliefors test will be used to examine whether the data are normally distributed. Data will be presented as percentages, mean (SD), or median (range) accordingly. The 1-tailed unpaired Student *t* test and Pearson *χ*^2^ test (or the Fisher exact test) will be used to make comparisons between different groups. The OS and progress-free survival curves will be plotted using the Kaplan-Meier method, and a comparison of the two groups will be performed via the log-rank test. The influencing factors will be analyzed by univariate and multivariate Cox proportional hazards regression. Statistical significance is set at *P*<.05. The survival prediction model will be established by multivariate Cox regression models and the Kaplan-Meier survival curves. The predictive ability of the final model will be evaluated using the Harrell concordance index (C-index) and calibration curves.

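### Operative and postoperative variables are lined up as ordinary Cox covariates for a whole-cohort survival model, and the abstract promises odds ratios where Cox regression gives hazard ratios

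*Protocol article*

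**What the plan says.** All places are in the Protocol article.

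- **Introduction, Objective.** The prognostic factors to be analysed are described as "such as treatment modalities, tumor subtypes, pre- and postoperative neurological function, and more".
- **Exposure Measures.** Beside demographic and clinical variables, the exposures of interest include this group: "Treatment-related factors include operation approach, operation time, blood loss, postoperative hospital stay, adjuvant therapies, etc".
- **Abstract, Objective.** The survival prediction model is to be built on the prognostic factors that the study identifies.
- **Sample Size and Study Timeline.** "there are 12 predictive factors we plan to analyze in the prediction model", for which "100 cases in each group are needed". The 12 are not named.
- **Primary Outcome.** Overall survival runs from the first antitumor treatment for the spinal metastases to death from any cause.
- **Statistical Analysis.** The two groups are compared by Kaplan-Meier curves and the log-rank test. Influencing factors are studied by Cox regression, singly and jointly, and the prediction model comes from the joint Cox model. No landmark, time-dependent or surgery-only analysis is mentioned.
- **Abstract, Methods.** Directly after the Cox regression: "Odds ratios with 95% CIs will be presented".

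**The concern.** A Cox model with fixed covariates assumes that every value is known at time zero for every patient in it. Several of the listed variables fail one or both parts of that condition.

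**Timing.** Neurological status after surgery, length of stay, and adjuvant treatment given after the first therapy are observed only in patients who live long enough to have them. Entered as if known at the start, they credit the time survived before measurement to the value measured later. The estimated effects are then biased.

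**Definition.** Surgical approach, operating time, blood loss and postoperative stay have no value in a patient who was not operated on. Half of the planned cohort is in that position.

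**Use.** A prediction that needs operating time or postoperative neurology cannot be made when surgery is being considered, which is when a model meant to guide surgeons would be wanted.

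Separately, Cox regression estimates a hazard ratio. If the result is labelled an odds ratio, a reader will take it for a different quantity.

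**Working it through.** **1. The plan's own figures.** The figure for this model is 100 per group for 12 factors. The article gives no formula, event rate or events-per-factor target, so it can be neither reproduced nor refuted; 200/12 = 16.7 patients per factor. The separate figure for the group comparison does reproduce. The inputs are "the average OS time was 11 (SD 4) months in the surgical group and 9 (SD 3) months in the nonsurgical group" and "Assuming an overall Type 1 error (α) of .05 and Type II error (β) of .1, we need 66 patients in each group". With two-sided α = 0.05 and 90% power, n = (4² + 3²)(1.960 + 1.282)²/2² = 65.67, which rounds up to 66.

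**2. When each variable is known, and in whom.**

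| Variable | Known at time zero? | Defined in nonsurgical patients? |
|---|---|---|
| Surgical approach, operating time, blood loss | Only if surgery is the first antitumor treatment | No |
| Postoperative length of stay | No | No |
| Postoperative neurological function | No | No |
| Adjuvant therapy | The first therapy given, yes; later therapy, no | Yes |

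**3. What a joint model does with an operative variable.**

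- *Left missing.* A complete-case fit drops all 120 nonsurgical patients of 240.
- *Filled with a code.* Give nonsurgical patients a "none" category for surgical approach, and the surgical categories add up exactly to the surgery indicator, so the two cannot be separated. Give them zero for blood loss or operating time with treatment group in the model, and the group coefficient becomes the contrast at zero blood loss or zero operating time. Leave group out, and the operative variable absorbs the group difference.

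**4. Size of the loss in the complete-case route.** Followed patients: 120 × 0.80 = 96 per group, 192 in all. The article gives no death proportion at 24 months, so I assume exponential survival and read 11 and 9 months in two ways.

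- As means: 1 − exp(−24/11) = 0.887 and 1 − exp(−24/9) = 0.931. Deaths: 96 × (0.887 + 0.931) ≈ 174.5, of which 85.2 are surgical. With 12 factors: 174.5/12 = 14.5 deaths per factor in the whole cohort and 85.2/12 = 7.1 in the surgical group alone.
- As medians: 0.780 and 0.843. Deaths: about 155.7, of which 74.8 are surgical. Per factor: 13.0 and 6.2.
- For any assumed death proportion from 50% to 100%: 192 × 0.5/12 = 8.0 to 192/12 = 16.0 in the whole cohort, against 96 × 0.5/12 = 4.0 to 96/12 = 8.0 in the surgical group.

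The roughly twofold fall does not depend on the survival assumption, because half the patients go.

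**5. Odds ratio against hazard ratio.** With exponential survival and means of 11 and 9 months, surgical against nonsurgical:

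- HR = (1/11)/(1/9) = 9/11 = 0.82.
- OR for death at 12 months = (exp(12/11) − 1)/(exp(12/9) − 1) = 0.71.
- OR for death at 24 months = (exp(24/11) − 1)/(exp(24/9) − 1) = 0.59.

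The hazard ratio is one number, while the odds ratio moves with the time point. They are not interchangeable.

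**The case against.** The best defence is that Exposure Measures lists what will be collected and does not specify a model. The article never says that every item enters the Cox regression, and operative variables could be analysed within the surgical group alone. That is right as far as it goes. But the Objective names postoperative neurology as a prognostic factor, the abstract builds the model on the prognostic factors, and the only method given for them is ordinary Cox regression. Followed as written, the text leads to the problem.

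The timing argument also has limits. If surgery is the first antitumor treatment, operating time and blood loss are fixed on day zero and conditioning on survival is negligible. For nonsurgical patients the first therapy itself defines time zero. The argument holds for length of stay, postoperative neurology, later adjuvant therapy, and operative values when other treatment came first.

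A reader might infer three stronger things that the article does not support:

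- *That far more than 12 factors enter the model.* The sample size section says 12. The longer exposure list is not called a covariate list, and no univariate selection rule is given.
- *That the model is judged only on the data it was fitted to.* The text is "The predictive ability of the final model will be evaluated using the Harrell concordance index (C-index) and calibration curves", which does not say on which data. A condensed article may leave resampling or other validation to the full protocol or analysis plan.
- *That the surgery effect will be adjusted away through its own consequences.* The comparison of the groups is by Kaplan-Meier and log-rank; no Cox coefficient is named as the treatment estimate.

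Finally, the odds-ratio wording stands only in the abstract. It is a plain error there, and a small one to correct.

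**Conclusion.** The point holds for the prognostic and prediction modelling, not for the log-rank comparison of the groups. As written, the article allows values that arise after time zero, and values that exist only in operated patients, to enter a whole-cohort Cox model as fixed covariates. Estimates for those variables would be biased by conditioning on survival, and the model would not be usable before treatment.

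One operative covariate handled by complete cases would cut the followed sample from 192 to 96 and about halve the deaths per factor, from 13.0–14.5 to 6.2–7.1 with 12 factors. The halving follows from the 1:1 design. The absolute values rest on assumed exponential survival and 80% follow-up. The size of the survival-conditioning bias cannot be derived from the article: it depends on early deaths and on when each value is recorded, and neither is given.

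The odds-ratio statement is wrong on its face. The values 0.82, 0.71 and 0.59 illustrate the gap under the same exponential assumption.

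**What to change.** 1. Restrict the whole-cohort prediction model to the 12 planned factors, chosen from variables measurable before the treatment decision in both groups.
2. Analyse operative variables, length of stay and postoperative neurology within the surgical group only, counting survival from a landmark such as discharge. Patients who die before the landmark do not contribute, and this should be stated. With roughly 75 to 85 surgical deaths on the assumptions above, this analysis should stay small.
3. Enter adjuvant therapy that starts after time zero as a time-dependent covariate.
4. In the abstract's Methods, replace odds ratios with hazard ratios.

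No new data are needed. The cost is a change of wording and a little more analysis work.

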### Patient Enrollment and Group Allocation

All patients with SMLC being treated at our center are potential candidates, and those who meet the inclusion and exclusion criteria will be eligible for enrollment in our study. Patients who receive surgical treatment along with postoperative systemic comprehensive treatment will be enrolled in the surgical group. Patients who receive only conservative treatment (eg, radiotherapy, chemotherapy, targeted molecular therapy, immunological therapy, etc) without surgical treatment will be enrolled in the nonsurgical group. All study procedures, as well as the participants’ rights, responsibilities, benefits, and risks, will be communicated, and participants will sign an informed consent form. Figure 1 displays the study flowchart.

In order to participate, patients will need to meet certain eligibility criteria. The inclusion criteria are (1) a pathological diagnosis of SMLC, (2) understanding and voluntarily participating in the study, and (3) being regularly followed up beyond 2 years or to the endpoint. Exclusion criteria include: (1) not receiving antitumor treatment at our hospital, (2) coexistence of spinal trauma or infection, (3) history of other malignancies, and (4) unwillingness to participate or inability to adhere to our follow-up schedule.

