### Outcomes

#### Primary Outcome

The primary outcome metric of the study is the OS period. OS is defined as the time after the start of any antitumor therapy for SMLC to death of any cause.

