As our understanding of the molecular biology of lung cancer increases, many mutated targets are being identified, including the epidermal growth factor receptor (EGFR), anaplastic lymphoma kinase, ROS1, BRAF V600E mutation, etc [6,7,27,28]. Targeted drugs can act directly on these specific mutations and diminish tumor cells. Dohzono et al [29] compared the median OS of patients with SMLC receiving or not receiving EGFR tyrosine kinase inhibitors and found the former group enjoyed a longer OS period (21.4 months vs 6.1 months). In recent years, the application of some immunotherapeutic drugs has proven to be effective [7]. The concept of immunotherapy is to introduce specific blockers to inhibit some immunological signaling paths that are related to the development and metastasis of tumors. Currently, anti-PD-1 and anti-PD-L1 antibodies have been recognized as the choice of care for some advanced lung cancers after the failure of first-line cytotoxic therapy [30]. Borghaei et al [28] found that the median OS period of PD-L1(+) patients who received specific targeted blockers was longer than that of PD-L1(–) patients (17.7 months vs 10.5 months). Furthermore, systematic use of bone-targeted agents (eg, bisphosphonates and denosumab) has significantly reduced devastating spinal-related events, such as paralysis and loss of self-care ability [31].

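### No stated provision adjusts the surgical v nonsurgical survival comparison for antitumor treatment received before therapy for spinal metastases

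*Protocol article*

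**What the plan says.** **Eligibility** (Patient Enrollment and Group Allocation). The source population is wide: "All patients with SMLC being treated at our center are potential candidates". The inclusion list opens: "The inclusion criteria are (1) a pathological diagnosis of SMLC, (2) understanding and voluntarily participating in the study". Its third item concerns follow-up. Of the four exclusions, three read: "1) not receiving antitumor treatment at our hospital, (2) coexistence of spinal trauma or infection, (3) history of other malignancies". The fourth concerns willingness and adherence. The first exclusion is about where treatment is given, not about what came before.

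**Time zero** (Primary Outcome). "OS is defined as the time after the start of any antitumor therapy for SMLC to death of any cause". Lung cancer treatment given before the spinal disease was treated therefore lies before the clock starts.

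**Variables** (Exposure Measures). The treatment sentence is "Treatment-related factors include operation approach, operation time, blood loss, postoperative hospital stay, adjuvant therapies, etc". The tumor items are "tumor factors (pathology, gene detection, tumor segments, and metastatic status". The clinical items include onset time, performance status, neurological function, pain and ambulation. Prior systemic therapy, prior radiotherapy, line of therapy and earlier drug failure are not named. Nor is whether the spinal disease was present when the lung cancer was first diagnosed.

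**Allocation and analysis** (Treatment; Statistical Analysis). A multidisciplinary team decides on surgery. The OS and progression-free survival (PFS) curves of the two groups are compared by log-rank test. Univariate and multivariate Cox regression is planned for influencing factors. The 12 predictors mentioned under Sample Size and Study Timeline are not named.

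**The concern.** A patient whose spinal metastasis is found at first diagnosis, with no drug yet used, enters at the same time zero as a patient whose spinal disease appeared after earlier treatment had failed. Their expected remaining survival may well differ. Randomisation would balance this on average, but a team decision on clinical grounds need not. If the pretreated share differs between groups, the log-rank test reads part of that difference as an effect of surgery.

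The Cox regression does not clearly close the gap. It is described as a search for influencing factors, its covariates are not fixed in the text, and treatment history is not among the measures from which they would be drawn. A survival prediction model built from the named measures would also lack the variable, whether or not the groups are balanced on it.

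**Working it through.** **1. The effect the plan is sized for.** Sample Size and Study Timeline gives mean OS 11 (SD 4) v 9 (SD 3) months, α = .05, β = .1 and 66 per group. Two-sided: n = (1.960 + 1.282)² × (4² + 3²) / 2² = 10.507 × 6.25 = 65.67, rounded up to 66. The figure reproduces, so the benchmark is a 2-month difference. If the means are read as exponential, the corresponding hazard ratio is about 9/11 = 0.82, or 11/9 = 1.22 inverted. That reading is rough, because SDs of 4 and 3 are far smaller than an exponential distribution would give.

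**2. Assumptions for the illustration; none is a document value except the 120 per group.**
- No true surgical effect, and exponential survival within each stratum.
- Overall mean OS 10 months (midway between 11 and 9), censoring at 24 months, 120 per group.
- Hazard ratio h, pretreated v untreated: 1.5, 2.0 or 2.5.
- Pretreated share 50% v 30%, or 60% v 30%.

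**3. Formulas.** With p̄ the average of the two shares, the untreated mean is m = 10 / [1 − p̄(1 − 1/h)]. The 24-month restricted means are R₀ = m(1 − e^(−24/m)) for untreated and R₁ = (m/h)(1 − e^(−24h/m)) for pretreated patients. The apparent group difference is (difference in shares) × (R₀ − R₁).

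Worked case, h = 2 and 50% v 30%:
- m = 10 / (1 − 0.4 × 0.5) = 12.5.
- R₀ = 12.5 × (1 − e^(−1.92)) = 10.67.
- R₁ = 6.25 × (1 − e^(−3.84)) = 6.12.
- Difference = 0.20 × (10.67 − 6.12) = 0.91 months.

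**4. Results.** Apparent hazard ratio (HR) and log-rank rejection rate come from 2,000 simulated studies per setting. HR is for the group with more pretreated patients.

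| h | Shares | m | Apparent HR | Difference to 24 months | Log-rank rejection (nominal 5%) |
|---|---|---|---|---|---|
| 1.5 | 50 v 30 | 11.54 | 1.08 | 0.55 | 9.0% |
| 1.5 | 60 v 30 | 11.76 | 1.13 | 0.83 | 14.2% |
| 2.0 | 50 v 30 | 12.50 | 1.14 | 0.91 | 16.2% |
| 2.0 | 60 v 30 | 12.90 | 1.22 | 1.38 | 31.4% |
| 2.5 | 50 v 30 | 13.16 | 1.17 | 1.17 | 21.4% |
| 2.5 | 60 v 30 | 13.70 | 1.28 | 1.77 | 44.0% |

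Solving the population Cox score equation numerically for the same settings gives hazard ratios within 0.01 of these.

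**5. Cross-check from another starting point.** Take a median of 11 months in untreated patients and more pretreated patients in the nonsurgical group. With h = 2, shares of 40% v 60% and 30% v 60% give an apparent surgical HR of 0.88 and 0.82, the inverses of 1.14 and 1.22. A 10-point imbalance (40% v 50%) gives 0.96, 0.94 and 0.92 for h = 1.5, 2.0 and 2.5. With equal shares the HR is 1 and the difference in months is 0.

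**The case against.** The strongest reply is that silence in a condensed article is not absence from the study. The treatment list ends in an et cetera, the objective leaves its list of prognostic factors open, the 12 predictors are unnamed, and the visit task list is in an appendix that is not shown. A reader might infer that prior treatment is not recorded, that the analysis cannot adjust for it, or that the prediction model omits it. The documents support none of these; they support only that it is not named. What remains is that eligibility is given as numbered lists, that Exposure Measures is itemised down to height and x-ray, and that every treatment factor it names is operative or adjuvant.

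Second, some listed items may act as partial proxies: onset time, metastatic status, genotype and performance status. Onset time is not defined, so it cannot be shown either to capture or to miss the point. Adjusting for these items could remove part of any bias. The illustration has no covariates and speaks only to the unadjusted comparison.

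Third, a reader might take the Discussion as evidence of the size of the effect. It reports a median OS of 21.4 v 6.1 months with and without EGFR inhibitors, and describes immunotherapy as "the choice of care for some advanced lung cancers after the failure of first-line cytotoxic therapy". The first compares drugs received, and the second says when a drug class is used. Neither compares pretreated with untreated patients, so neither supports any particular hazard ratio.

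Fourth, a reader might infer that the bias in months could exceed the whole planned effect. That needs means followed without limit, (difference in shares) × m × (1 − 1/h), which run from 0.77 to 2.47 months. Restricted to 24 months, every setting stays below 2 months. On the hazard-ratio scale the two 60% v 30% settings with h of 2.0 and 2.5 do reach or pass 1.22, but only on the rough exponential reading of the planned effect.

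**Conclusion.** The point holds in a limited form. Entry is not restricted by prior antitumor treatment, OS starts at the first therapy for SMLC, treatment history is not named among the exposure measures, and the stated group comparison is an unadjusted log-rank test in non-randomised groups. No stated provision therefore adjusts the main comparison for a plausible confounder.

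How large the bias is, and which group it favours, cannot be known from the documents. The apparent HR of 1.08 to 1.28 (or its inverse) and the 0.55 to 1.77 months rest wholly on the assumed hazard ratios and a 20 to 30 point imbalance. They show that a bias of the same order as the planned effect is possible, not that it is likely. The group comparison has no such bias if the shares are equal. The gap should be closed while enrollment, planned to run to June 2027, is still open.

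**What to change.** 1. Name two baseline items in Exposure Measures: (a) SMLC present at first lung cancer diagnosis v arising during or after treatment; (b) number of systemic lines before time zero, and whether a targeted or immune drug had already failed.
2. Abstract both from charts for all patients, including those already enrolled. If they are already collected, one sentence saying so is enough.
3. Prespecify them as covariates or strata in an adjusted Cox comparison of OS and PFS between the groups, reported beside the log-rank test.
4. List them as candidate factors for the prediction model, if they are not already among the 12.

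The cost is a few chart-abstraction fields per patient and one or two model degrees of freedom. No visit is added and no treatment changes.
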